### Case definitions

Leprosy and LR are clinical diagnoses, based on assessment by (an) experienced physician(s) or healthcare worker.

**MB leprosy** is based on the WHO definition of six or more skin lesions, or a positive slit-skin smear with demonstration of
*M. leprae*, irrespective of the number of skin lesions
^
54
^.

A
**LR** is defined as the occurrence of T1R or T2R according to below case definitions:

**T1R** characterized by increased inflammation (erythema and oedema) of pre-existing skin lesions and/or neuritis. Participants may have a skin or nerve reaction only or have both at the same time.

**T2R** is based on the appearance of crops of tender, erythematous cutaneous and subcutaneous nodules anywhere on the body. Systemic features may be present, but are not obligatory: fever (temperature > 38°C), neuritis, joint and muscle pain, bone tenderness, oedema, malaise, anorexia, lymphadenitis, orchitis, iridocyclitis, uveitis or glomerulonephritis
^
52
^.

**Neuritis** is defined as spontaneous nerve pain, paraesthesia or tenderness which may or may not be associated with NFI (within the last six months)
^
55
^.

**NFI** is defined as clinically detectable impairment of protective sensory or motor nerve functions that originated within the last six months and necessitates intervention, not necessarily associated with neuritis (silent or asymptomatic neuropathy
^
56
^).

**Sensory loss** is defined by a decrease in sensation as measured by Semmes Weinstein monofilament testing. In the hands, this is defined as not being able to perceive the 2g monofilament at 2 points out of 3 sites in each nerve of the hand. In the feet, this is defined as not being able to perceive the 10g monofilament at 3 out of 4 sites of the foot
^
55,
57
^. The thenar area for the median nerve function, the hypothenar for the ulnar nerve function, and the plantar aspect of the foot for the posterior tibial nerve function will be assessed.
**Motor loss** is defined by a decrease in voluntary muscle testing score, by 1 point or more from the normal score of 5, using the modified Medical Research Council (MRC) Scale.

### Clinical severity scales

We will use two severity scales that have been prospectively validated in different endemic settings and used in previous clinical trials
^
52,
53,
55,
58–
60
^:

**T1R:** Modified Clinical Severity Score is used to assess T1R severity. The Score includes 19 items and is expressed as a numeric score (range score 0-48). The maximum score possible for skin (A), sensation (B) and motor function (C) are 9, 9 and 30, respectively. The skin, sensory and motor scores will be summated for each patient per study visit
^
60
^.

**T2R:** ENLIST ENL Severity Scale (EESS), including 10 items evaluating multiple organs, and expressed as a numeric score (0 to 30) and classified as mild (≤8) or severe (≥9)
^
52
^.

### Inclusion/exclusion criteria

Participants will be considered eligible for enrolment in this trial if they fulfil all the inclusion criteria and none of the exclusion criteria. The trial will enrol participants aged between 18–65 years presenting with newly diagnosed MB leprosy and who have no LR and/or NFI with indication for corticosteroids at the time of diagnosis or trial enrolment. Screened participants who are not eligible will be recorded in a screening log with reasons for screening failure, and will receive local standard-of-care.

**
*Inclusion criteria*
**

Participant aged ≥18 and ≤65 years.Participant is newly diagnosed with MB leprosy and receiving MDT ≤28 days.Participant is willing and able to give informed consent for participation in the trial.Participant is willing to adhere to study follow-up schedule for 48 weeks.

**
*Exclusion criteria*
**

Participant has received MDT >28 days for the current episode of MB leprosy, prior to study enrolment.Presence of leprosy reaction or nerve function impairment requiring systemic corticosteroids on screening or enrolment evaluation.Participants who have been treated for leprosy in the past.Chronic systemic corticosteroid use for any other medical condition on screening evaluation (chronic use defined as ≥ 2 weeks).History of diabetes mellitus or diabetes mellitus diagnosed on screening evaluation (random blood glucose is elevated ≥200 mg/dL (or ≥11,1 mmol/L) or fasting blood glucose ≥ 126 mg/dL (or ≥7.0 mmol/L)).History of hypoglycaemia (random blood glucose <55 mg/dL (or <3.0 mmol/L)).History of cardiac failure, ischaemic heart disease, alcoholism, history of lactic acidosis or states associated with lactic acidosis such as shock or pulmonary insufficiency, and conditions associated with hypoxia.History of intolerance or hypersensitivity to metformin.Estimated glomerular filtration rate (eGFR) ≤30 mL/min/1.73m
^2^, calculated by the CKDEPI equation, on screening evaluation
^
61,
62
^.ALT/SGPT ≥3 times the upper limit of normal (ULN) on screening evaluation.HIV-positive on screening evaluation (screening applicable for sites in Papua only
^
a
^).Female participant in childbearing age who is pregnant (clinically confirmed or urine dipstick for human chorionic gonadotrophin hormone) or breastfeeding on screening evaluation.Use of metformin within 12 weeks prior to study enrolment.Use of other regular hypoglycaemic agents, including insulin, on screening evaluation.Participation in another research trial involving an investigational product within 12 weeks prior to study enrolment.

### Randomisation and treatment allocation

**
*Randomisation*
**

All participants who present with newly diagnosed MB leprosy and agree to participate in the trial, will be screened for eligibility. Participants eligible for enrolment, will be randomized to two parallel groups in a 1:1 ratio: metformin for 24 weeks versus identical placebo for 24 weeks. Placebo will be identical in appearance to active drug and contain the inactive ingredients sodium carboxymethyl cellulose, hypromellose and magnesium stearate. It will be dosed and dispensed in the same way as metformin. Randomization will be stratified by BI-score (BI ≥ or < 4) and study site. The randomization list will be computer-generated based on random permuted blocks with variable block size. The randomization list will be generated through a statistical code and securely incorporated within the trial database. Based on the randomization list blinded drug packages (treatment packs are labelled with a different code per site) are distributed to all study sites. A 24h web-based randomization service is provided through
REDCap. Treatment should start as soon as possible after randomization. Unblinding will be performed after the data collection, statistical analysis plan and statistical coding have been completed, or earlier at the individual level, if this is essential for best management of the participant and agreed upon by the Site Principal Investigator (PI) and Chief Investigators. Study medication must be discontinued for an individual after unblinding. All instances of unblinding should be reported to the Data Monitoring Committee (DMC).

**
*Blinding*
**

Identical vials of metformin or placebo tablets will be prepared by the Trial Pharmacist at OUCRU ID’s Clinical Trial Unit. The Trial Pharmacist will make up and label individual-participant blinded treatment packs with trial numbers, containing either active drugs or identical placebo sufficient for 6 periods of 4 weeks of treatment according to the prespecified randomization list. No other study team members including PI, study coordinators and site PI’s, doctors, nurses, laboratory technician’s and pharmacist’s have access to the key of the randomization list.

**
*Treatment discontinuation*
**

The participants may request for any reason to withdraw consent for treatment or the investigator may discontinue treatment for any of the following reasons:

An AE which requires discontinuation of the investigational medicinal product (IMP,
Table 1).Pregnancy confirmed by urine dipstick for human chorionic gonadotrophin hormone.Request of clinical team if believed the IMP is no longer in the best interest of the patient.

**Table 1. T1:** Overview of adverse events that require discontinuation of Investigational Medicinal Product.

Adverse events
• Severe acute renal impairment (estimated glomerular filtration rate (30mL/min/1.73m ^2^)
• Lactate ≥ 3 mmol/L and/or onset of metformin-related lactic acidosis (testing triggered in case of clinical suspicion)
• Severe liver involvement: alanine transaminase (ALT) > 3x upper limit normal (ULN), if suspected metformin-associated, or ALT > 4x ULN
• Hypoglycaemic episode (blood sugar < 3.9 mmol/L OR < 70 mg/dL)
• Severe diarrhoea (≥ 5 stools/day with signs of dehydration)
• Mild/moderate diarrhoea, vomiting and/or epigastric pain, if persistent and patient is uncomfortable (despite dose reduction)

### Data collection

Participants will be enrolled in the trial for a total of 48 weeks. Treatment with metformin or placebo (IMP) is the only intervention used in the MetLep Trial. During the first two weeks, adjunctive metformin hydrochloride 500mg extended-release tablets or matched placebo will be given once daily, escalating to 1000mg metformin hydrochloride extended-release tablets or placebo once daily for another 22 weeks, in addition to standard-of-care MDT. The total duration of IMP intervention will be 24 weeks, while the total duration of MDT will be 48 weeks complying to WHO and national guidelines (
Figure 1). Appropriately trained clinicians and/or nurses with experience in the management of leprosy will be responsible for clinical care. In principle, participants will be reviewed every four weeks (accumulating to a total of 15 visits spread over 48 weeks) to assess the response to treatment, the development of LR and other outcome measures (more details in
Table 2). Home visits may be used to minimise inconvenience for participants. In case of clinical deterioration (i.e. adverse events, LR), additional unscheduled visits may occur. Study participants who develop a LR will receive appropriate anti-inflammatory treatment according to national guidelines. Participants who miss follow-up visits will be contacted by phone. Clinical and laboratory data (including AEs) will be entered into an electronic REDCap database hosted by OUCRU ID. REDCap is a secure, web-based application designed to support data capture for research providing audit trails for tracking data manipulation.

**Table 2. T2:** Schedule of clinical procedures and laboratory investigations.

	**Screening**	**W0** **Enrolment**	**W2**	**W4**	**W8**	**W12**	**W16**	**W20**	**W24**	**W28**	**W32**	**W36**	**W40**	**W44**	**W48** **Completion of MDT**	**LR (Any time point)**	**Minimum number of visits**
**Visit no**	V00	V01	V02	V03	V04	V05	V06	V07	V08	V09	V10	V11	V12	V13	V14	VLR	15
Patient information and informed consent	X																1
Registration Study ID	X																1
Eligibility criteria assessment	X																1
Randomisation		X															1
Initiation IMP		X															1
Increase dosage IMP			X														1
**Clinical history and examination**																	
Past medical history		X															1
Current signs & symptoms		X	X	X	X	X	X	X	X	X	X	X	X	X	X	X	14
Physical examination ^ a ^		X	X	X	X	X	X	X	X	X	X	X	X	X	X	X	14
Adherence to treatment ^ b ^		X	X	X	X	X	X	X	X	X	X	X	X	X	X	X	14
Adverse events assessment			X	X	X	X	X	X	X	X	X	X	X	X	X	X	13
T1R/T2R assessment/Severity Scale			X	X	X	X	X	X	X	X	X	X	X	X	X	X	13
Quality of life assessment		X				X			X						X	X	4
Study termination form															X		1
Participant feedback survey															X		1
**Clinical Routine Investigations**																	
Full blood count	X																1
Serum creatinine	X																1
ALT	X																1
Blood glucose ^ c ^	X																1
Fingerprick glucose test			X	X	X	X	X	X	X								7
HIV-test ^ d ^	X																1
Pregnancy test (childbearing age women)	X																1
Slit skin smear	X								X						X		3
**Research Samples**																	
Skin biopsy (6 mm)		X														X	1
Serum (4 mL)		X	X	X		X			X			X			X	X	7
EDTA blood (4 mL)		X		X		X			X							X	4
PAXgene® tube (2.5 mL)		X	X													X	2
Total blood volume for research (mL)		10.5	6.5	8		8			8			4			4	10.5	49

In addition to the scheduled study visits at fixed timepoints (outlined above), additional unscheduled visits may take place in case of a LR, adverse events or any other medical complaints and will be recorded as such. Abbreviations: ALT, alanine transaminase; ID, identification; IMP, investigational medicinal product; LR, leprosy reaction; MDT, multi-drug therapy. a. Physical examination includes body weight, height, blood pressure and nerve function assessment, incl. nerve palpation, sensory testing with five Semmes-Weinstein monofilaments at designated test sites on hands and feet and voluntary muscle power graded using the modified Medical Research Council scale. b. Assessment of treatment adherence to IMP (until week 24) and MDT (to week 48). c. Suspect for diabetes: if random blood glucose is elevated ≥200 mg/dL (or ≥11,1 mmol/L) or fasting blood glucose ≥ 126 mg/dL (or ≥7.0 mmol/L). d. HIV-screening only applicable for participants in Papua.

**
*Clinical assessments*
**

During each study visit the following procedures will be undertaken (
Table 2):

■ Systematic evaluation of clinical symptoms and physical examination including nerve function assessment established through nerve palpation, sensory testing and voluntary muscle testing.■ Assessment of adherence to IMP (until week 24, W24) and MDT (until W48) through (i) a brief adherence questionnaire; (ii) pill counts on pharmacy records; and (iii) collection of treatment diaries and distribution of new diaries to each patient by the pharmacist; and (iv) clinical criteria hyperpigmentation and ichthyosis (extensor surfaces).■ Record all AEs and SAEs during the first 24 weeks when IMP is given. The severity and likely relationship of these AEs to metformin will be assessed and documented by the study team, chief investigators and/or study coordinator.■ Assessment of LR and its severity using standard case definitions and validated severity scales
^
52,
53
^.■ Assessment of QoL-questionnaires (at pre-specified study visits).

**
*Laboratory assessments*
**

Full blood count, serum blood glucose, creatinine and ALT will be performed at screening to rule out diabetes mellitus and detect any other relevant abnormalities. Slit skin smears will be performed at W0, W24, and W48 as part of routine clinical care. For participants who have provided consent, a skin biopsy will be performed at W0. From follow-up visit W2 until W24 a fingerprick glucose test will be performed to rule out hypoglycaemia as an additional preventive measure. During any follow-up visits, participants may undergo additional laboratory evaluation for signs or symptoms of potential (S)AEs at discretion of the study team. In case of a LR, a skin biopsy to confirm the diagnosis plus additional blood samples will be performed for bioarchiving.

**
*On-site biobanking for future in-depth analysis*
**

The standard participant informed consent form will request consent from participants for genetic analysis as well as biological sample storage for future, ethically approved research. Any proposed plans to use samples other than for those investigations detailed in this protocol will be submitted to the relevant ethics committees prior to any testing. Blood samples (serum and stimulated, heparinized whole blood) and skin biopsies will be stored for future analyses according to the schedule of procedures (
Table 2). Skin biopsies will be used for histopathology,
*M. leprae* strain typing, AMR analysis, and, if possible, WGS. Feasibility and range of these additional assays will depend on available funding and emerging scientific insights. The identification and investigation of immunopathogeneis of infection is a rapidly developing research field and novel technologies will likely be identified by the global scientific community during the time period of this study. Therefore, once study samples at serial intervals are available, we will prioritize assays that are most likely to lead to novel insights and patient benefit. Further testing approaches will be driven by advances in diagnostic technologies, such as low complexity multibiomarker tests, genomics, proteomics, metabolomics and/or transcriptomics
^
63–
65
^.

**
*Quality control*
**

Internal and external site monitoring will be carried out at each site to ensure human subject protection, study and laboratory procedures, and data collection procedures meet the international committee of harmonisation (ICH) regulatory guidelines. University of Oxford as the sponsor, represented by the Oxford University Clinical Research Unit Indonesia (OUCRU ID), is responsible to ensure the oversight of the clinical trial conduct and adherence to the protocol. The frequency, type and intensity of routine monitoring and the requirements for triggered monitoring are detailed in the Monitoring Plan. The monitoring will adhere to the principles of ICH good clinical practice (GCP) and the Monitoring Plan. The study may be subject to inspection by the Indonesian drug regulatory authority (BPOM RI) to ensure adherence to GCP and other assessment by relevant institution(s)/authority(ies), e.g. local ethics committee.

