^. Metformin does not cause hypoglycaemia in normoglycemic individuals. Rifampicin may enhance the glucose-lowering effect of metformin in non-diabetic individuals by increased hepatic expression of OCT1, resulting in increased metformin delivery to the liver
^
70
^. Importantly, the combination of rifampicin plus metformin did not reduce baseline blood glucose values or cause hypoglycaemia and rifampicin exerts a countervailing effect by boosting intestinal glucose absorption. A study in TB-patients with DM reported that rifampicin increased metformin plasma levels with 17–30%, but did not alter blood glucose levels
^
71
^. The interaction between rifampicin and metformin, however, will be of less significance in our population, as rifampicin is only given once a month at a dose of 600 mg, whereas in TB it is given daily. No interactions are known between metformin and dapsone or clofazimine. We will minimize the risk of AEs in the trial by excluding candidates with a history of renal or liver insufficiency and DM, by counselling at enrolment and follow-up visits regarding the need to maintain adequate caloric intake, and counselling regarding the symptoms of hypoglycaemia and the actions to take if these symptoms occur.

**
*Dose modifications*
**

Possible IMP-related AEs will be managed in both randomized groups according to standard clinical practice. Additional requirement of the dose modification will be determined on a case-by-case basis by the attending physician according to the clinical circumstances and guidelines. If treatment is discontinued due to an AE, the investigator will arrange for follow-up visits until the AE has resolved or stabilised. Wherever possible, dose modifications should be performed without unblinding. Participants will not be put at any additional risk by trial randomization, as any participant who develops a suspected adverse drug reaction to the IMP will be managed as if they were receiving metformin.

**
*Safety reporting*
**

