The principles of ICH GCP apply to this study protocol. All grade 3 or 4, or serious AEs and adverse reactions (ARs), whether expected or not, will be recorded. Non-serious grade 1 or 2 AEs will only be recorded in case they are thought to be related to the IMP or if they result in a change or interruption in MDT. When an AE or AR occurs, the study team and site PI responsible for the care of the participant first assess whether or not the event is serious. If the event is serious and not only related to leprosy, or is fatal, then a SAE form must be completed and the coordinating centre (OUCRU ID) notified within 24 hours. The severity of all AEs and/or ARs (serious and non-serious) in this trial should be graded using the toxicity gradings following Common Toxicity Criteria for Adverse Events CTCAE version 5.0
^
72
^.

All AEs will be assessed for seriousness, causality and expectedness. Causality in relation to the IMP includes five categories: unrelated, unlikely, possible, probable, and definitely related. If the causality assessment is unrelated or unlikely to be related, the event is classified as an SAE. If the causality is assessed as possible, probable or definitely related, then the event is classified as an SAR. Expectedness of the AE is assessed using the summary of medicinal product characteristics (SMPC). An unexpected adverse reaction is one not previously reported in the current SMPC at the time the event occurred, or one that is more frequent or more severe than previously reported. If a SAR is assessed as being unexpected, it becomes a suspected unexpected serous adverse reaction (SUSAR).

All applicable SAE/SAR will be reported to the ethics committee and the Indonesian regulatory authority by OUCRU ID based on the requirements stipulated in the Head of BPOM RI Regulation No. 21 year 2015 on Clinical Trial Conduct (Peraturan Kepala Badan Pengawas Obat dan Makanan Republik Indonesia (BPOM RI) tentang Tata Laksana Uji Klinik); and/or relevant local regulations. Any applicable subsequent update to the regulation will be adhered to, respectively.

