The primary efficacy outcome is the proportion of participants experiencing a LR during study follow up (total 48 weeks). The effect measure is the treatment difference between the intervention (metformin plus MDT) and control (placebo plus MDT) group. The treatment difference will be quantified in a logistic regression model that includes BI as a continuous variable and study site. Results will be marginalized over BI and study site. We will also consider a model using a log-link, which provides risk ratios. If loss to follow-up is 5% or more, we will take censored data into account and fit the model using pseudo-values. The heterogeneity of the treatment effect will be assessed by including an interaction term between treatment and BI, as well as between treatment and study site (two separate models). For the safety outcome, the proportion of participants with at least one AE within the first 24 weeks will be compared. The chi-squared test will be used to compare the treatment arms, or Fisher’s exact test in case the expected number under the null hypothesis in at least one of the cells is smaller than one. The analyses to be performed will be documented in the Statistical Analysis Plan (SAP), which will be finalized before the database is unlocked and the final analysis with the unblinded data is performed. R software will be used.

**
*Analysis of the secondary outcomes*
**

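### Two conflicting AE recording rules can keep low fingerprick glucose readings, which Table 1 ties to stopping study drug, out of the safety outcomes

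*Protocol article*

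**What the plan says.** All references are to the protocol article.

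- **Measurement.** Data collection, Laboratory assessments: "From follow-up visit W2 until W24 a fingerprick glucose test will be performed to rule out hypoglycaemia as an additional preventive measure". In Table 2 the row "Fingerprick glucose test" is marked at W2, W4, W8, W12, W16, W20 and W24.
- **Status of a low value.** Table 1, the list of adverse events that require discontinuation of the IMP, includes "Hypoglycaemic episode (blood sugar < 3.9 mmol/L OR < 70 mg/dL".
- **Recording rule A.** Data collection, Clinical assessments: all AEs and SAEs are to be recorded in the first 24 weeks, with severity and relationship to metformin then assessed.
- **Recording rule B.** Adverse events and safety reporting, Safety reporting: grade 3 or 4 and serious events are always recorded, but "Non-serious grade 1 or 2 AEs will only be recorded in case they are thought to be related to the IMP", or where they lead to MDT being changed or interrupted.
- **Outcomes.** The primary safety outcome is the proportion with at least one AE to week 24, and secondary outcome 5 is the total number of AEs over the same period. No listed outcome names glucose or hypoglycaemia.
- **Analysis.** "For the safety outcome, the proportion of participants with at least one AE within the first 24 weeks will be compared". The AE total is compared by quasi-Poisson regression.

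**The concern.** Rules A and B cannot both define the set of AEs behind the primary safety outcome. Rule A has no causality filter. Rule B has one for every non-serious grade 1 or 2 event, and its only other trigger concerns MDT, not the IMP. Table 1, meanwhile, ties a low blood sugar to stopping the IMP. Under rule B a participant could therefore meet a Table 1 discontinuation criterion, have the event judged unrelated, continue MDT unchanged, and contribute nothing to either AE outcome.

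An event never recorded as an AE cannot be recovered by a later analysis of recorded AEs, however detailed. The trial's stated aims include tolerability and safety, and its results are meant to inform a Phase 3 trial, so the AE set should not depend on which paragraph a site follows.

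**Working it through.** **Step 1: the plan's own count.** Table 2 marks W2, W4, W8, W12, W16, W20 and W24, which is 7 tests. This agrees with the 7 in the row's last column. With 166 participants randomised 1:1, 166 / 2 = 83 per arm, 83 × 7 = 581 scheduled readings per arm and 166 × 7 = 1,162 in total.

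**Step 2: trace one low reading.** Take a reading below the Table 1 limit that is non-serious, grade 1 or 2, and leaves MDT unchanged.

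| Causality judgement | Rule A (Clinical assessments) | Rule B (Safety reporting) |
|---|---|---|
| Thought IMP-related | recorded | recorded |
| Thought unrelated, IMP continued | recorded | not recorded |
| Thought unrelated, IMP stopped under Table 1 | recorded | not recorded |

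The last row is the sharpest conflict: an event listed as an adverse event that requires discontinuation need not appear in the AE data.

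**Step 3: possible size.** The document gives no rate of low readings, so the rates here are assumptions. Let p be the proportion of an 83-person arm with such a reading and r the share judged IMP-related. Rule A records 83 × p participants; rule B records 83 × p × r.

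| p (assumed) | Rule A | Rule B, r = 0 | r = 0.25 | r = 0.5 | r = 1 |
|---|---|---|---|---|---|
| 2% | 1.66 | 0 | 0.42 | 0.83 | 1.66 |
| 5% | 4.15 | 0 | 1.04 | 2.08 | 4.15 |
| 10% | 8.30 | 0 | 2.08 | 4.15 | 8.30 |

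If blinding holds and r is the same in both arms, rule B multiplies any true risk difference in these events by r. At r = 0.5, half of it remains.

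**Step 4: precision of a count taken from the readings.** With the same assumed p in both arms, the approximate 95% half-width of the risk difference is 1.96 × √(2p(1−p)/83):

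- p = 2%: 1.96 × √(2 × 0.02 × 0.98 / 83) = 4.3 percentage points
- p = 5%: 1.96 × √(2 × 0.05 × 0.95 / 83) = 6.6 points
- p = 10%: 1.96 × √(2 × 0.10 × 0.90 / 83) = 9.1 points

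If no one in an arm of 83 had a low reading, the two-sided 95% upper limit would be 1 − 0.025^(1/83) = 4.3%. The comparison is descriptive and imprecise for modest differences.

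**Step 5: is a low reading an AE?** Table 1 gives a blood sugar limit but does not say whether a fingerprick value alone makes an episode. The exclusion criteria use another limit for another purpose: "History of hypoglycaemia (random blood glucose <55 mg/dL (or <3.0 mmol/L". CTCAE glucose grades are not reproduced in the document, so the share of low readings falling in grade 1 or 2 cannot be derived from it.

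**The case against.** The best defence has four parts.

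1. **Low readings do have a route into the results.** A reader might infer that no outcome or analysis uses them. That goes too far: once recorded as an AE, a low reading enters both the any-AE comparison and the AE count, and both are compared by arm. What stands is that entry depends on the recording rule.
2. **The SAP may tabulate AE types and glucose by arm.** A reader might infer that hypoglycaemia will go unreported by arm. The document cannot show this, because it defers the analyses to a SAP that is not at hand and the article condenses a fuller protocol. Tables of recorded AEs would still not restore events that rule B excluded.
3. **Rule A may be what sites follow, and the DMC sees unblinded data.** If rule A governs, nothing is lost. But the document does not say so, and rule B is the more detailed text. DMC access protects participants; it does not define the outcome.
4. **The fingerprick is a protective check, not an endpoint.** This is fair, and it argues against modelling mean glucose, which would be a preference and not a correction. It does not excuse an inconsistent AE set.

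A reader might also think that "Metformin does not cause hypoglycaemia in normoglycemic individuals" pushes assessors towards judging low readings unrelated. That is speculation. The same section says "Rifampicin may enhance the glucose-lowering effect of metformin in non-diabetic individuals", then plays that interaction down because rifampicin is given monthly, and it also provides for counselling on symptoms of hypoglycaemia. Gastrointestinal effects and lactic acidosis, not hypoglycaemia, are named as the main side-effects.

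**Conclusion.** The point holds as a contradiction in AE recording with a specific consequence. Clinical assessments and Safety reporting define different AE sets for the first 24 weeks, and the narrower one can drop a low fingerprick reading that Table 1 treats as grounds for stopping the IMP. If Safety reporting is followed, such a reading, when judged unrelated, is missing from the primary safety outcome and the total AE count. No listed outcome counts low readings directly.

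The size is unknown. Under assumed rates of 2% to 10% per arm, the number lost ranges from none (all judged related) to about 2 to 8 participants per arm (none judged related). This assumes that Safety reporting prevails, that a fingerprick value below the Table 1 limit counts as an adverse event, and that the events are non-serious, grade 1 or 2, and leave MDT unchanged. No sample-size or power figure changes. No view is taken on which glucose threshold or stopping rule is clinically right. The change is worth making because the rule is stated inconsistently and is cheap to repair, not because a harm has been shown.

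**What to change.** 1. **Reconcile Table 1, Clinical assessments and Safety reporting.** Define once the AE set that feeds the primary safety outcome and the total AE count, so that recording a Table 1 event does not depend on a causality judgement. State whether a fingerprick value alone is a hypoglycaemic episode for this purpose. Because enrolment is under way, also state which recording rule sites have applied so far.
2. **Count low readings from the readings themselves.** Report, by randomised arm, the number and proportion of participants with any W2 to W24 fingerprick reading below the protocol's own Table 1 limit, with a risk difference and 95% CI, whatever the causality judgement. The limit serves for counting only and implies nothing about clinical management.

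The cost is a wording amendment and one extra descriptive safety comparison, with no new test or visit. Clinical and laboratory data are to be entered in REDCap, so the count should also cover participants already past W24. The drawbacks are the wide intervals shown above and readings whose fasting state is not specified, which adds noise to both arms.
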